### 2.6. Interventions

#### 2.6.1. Initial Training

Before the start of the trial, all healthcare workers from the 24 study CSPSs will be invited to the Centre Muraz for a two-day training course on the epidemiology and clinical management of hepatitis B, the administration of HepB-BD, and the study protocol including how to obtain informed consent, to fill case report forms (CRF), and to obtain blood samples. Similarly, all medical doctors from the district hospitals of Dô and Dafra will be invited for a one-day training course on the clinical management of patients with chronic HBV infection and the study protocol.

#### 2.6.2. Control Period

During the control period, there will be no supply of the monovalent vaccines to the CSPS; therefore, babies born during this period in the catchment area of this CSPS will not receive HepB-BD.

#### 2.6.3. Interventional Period

Once a CSPS crosses from the control to the intervention period, the monovalent vaccines will be delivered from the district center to the CSPS and healthcare workers will start immunizing newborns. The delivery of HepB-BD will be integrated into a monthly supply chain for the routine infant vaccines. Babies born in the CSPS during the intervention period will receive HepB-BD immediately after birth. Those born at home during the intervention period will receive HepB-BD at the first contact with the CSPS at any time up to the time when the next dose of hepatitis B vaccine is scheduled (i.e., 8 weeks as a pentavalent vaccine) according to the WHO recommendation [21].

#### 2.6.4. Routine Care

All infants, irrespective of the study period, will receive three doses of pentavalent vaccine at 8-12-16 weeks as scheduled in the national immunization program. Screening of pregnant women for HBV infection is recommended in the country but not yet systematically conducted. In the study zone, none of the CSPSs and none of the district hospitals provide antenatal screening for HBV or the treatment of chronic HBV infection using antiviral therapy. Hepatitis B immune globulin (HBIG) is not available in the study area.

### 2.7. Outcomes

#### 2.7.1. Primary Outcome

-The risk of MTCT, defined as a prevalence of positive HBsAg in infants aged 9 months.

#### 2.7.2. Secondary Outcomes

-The coverage and timeliness of HepB-BD, pentavalent vaccines, and other vaccines recommended by the national infant immunization program.-The prevalence of anti-HBs ≥10 IU/L (or ≥100 IU/L) in infants aged 9 months.-The prevalence of HBsAg in mothers of children aged 9 months.-The prevalence of HBeAg in HBsAg-positive mothers.-The prevalence of HBV DNA levels ≥200,000 IU/mL in HBsAg-positive mothers.-Anthropology: the acceptability of adding HepB-BD into the infant immunization program among healthcare workers and community members.-Health economics: the public health benefits, the cost, and the cost-effectiveness of introducing HepB-BD into the infant immunization program in Burkina Faso versus the current situation.

### 2.8. Participant Flow

#### 2.8.1. First Visit (V1)

The participant flow is schematically presented in Figure 3. Whenever a pregnant woman visits a study CSPS for antenatal care, she will be assessed for her eligibility and will be invited to participate in the study. Women coming directly to a CSPS for delivery without a prior antenatal care visit will be invited to participate immediately after the child delivery. Using a participant information sheet written in French (Document S1) and an illustrated information sheet (Document S2), healthcare workers will explain the study to all potentially eligible pregnant women in a local language. Women aged ≥18 years will be asked to sign an informed consent (Document S3). Those aged <18 years will be asked to sign an assent, in addition to an informed consent form that will be signed by her legally authorized representative. Illiterate participants will be asked to provide a fingerprint. Once the informed consent is obtained, sociodemographic data will be collected through an interview with the women, and the case report form (CRF) for V1 will be filled (Document S4).

#### 2.8.2. Second Visit (V2)

The second visit takes place at the first contact between a mother–infant pair and the CSPS. V2 will be at the time of child delivery for women who give birth at the CSPS. For women who give birth outside the CSPS, V2 will be the first postnatal care visit to the CSPS. At V2, HepB-BD will be administered to an infant who was born after his/her CSPS has crossed over to the intervention period. In contrast, HepB-BD will not be given to an infant born before his/her CSPS has started the intervention. Data on the index pregnancy, childbirth, child’s date of birth and sex, and postnatal care, including whether and when HepB-BD was administered, will be collected on the CRF for V2 (Document S4).

#### 2.8.3. Third Visit (V3)

Mother–child pairs will be screened for HBsAg when the children return to the CSPS to receive the yellow fever vaccine and the first doses of the measles and rubella vaccines that are scheduled at the age of 9 months in Burkina Faso. Capillary blood will be obtained from mother–child pairs by finger-prick for a rapid diagnostic test (RDT) to detect HBsAg (DETERMINE™ HBsAg 2, Abbott, Abbott Park, IL, USA) [30,31] and DBS. The result of the HBsAg test will be immediately given to the participants on-site. Following the post-test counselling, 8 and 4 mL of blood will be drawn by venipuncture from the HBsAg-positive mother and HBsAg-positive child, respectively. The DBS from all participants and venous samples from those positive for HBsAg will be transferred to the Centre Muraz. Sera from infected mothers will be tested for alanine aminotransferase (ALT), aspartate aminotransferase (AST), HBV DNA PCR (RealTime HBV Viral Load Assay, Abbott), qHBsAg and qHBeAg (ARCHITECT, Abbott), HBeAg RDT (SD Bioline, Abbott), HBcrAg (Lumipulse, Fujirebio Europe, Gent, Belgium), and HBV-LAMP (Eiken Chemicals, Tokyo, Japan). Sera from infected children will be tested for ALT, AST, and HBV DNA. Vaccination history ascertained through the child vaccination card and HBsAg test result will be entered in the V3 CRF (Document S4). Participants identified to carry HBsAg will be given a next appointment to receive results of the laboratory tests (Figure 4), while V3 will be the final study visit for those testing negative for HBsAg. Hepatitis B vaccinations will not be systematically offered to HBsAg-negative women, because the vast majority of adults in Burkina Faso have been in contact with HBV during childhood, resulting in the prevalence of total hepatitis B core antibodies (anti-HBc) exceeding 70–80% in adults [32,33].

#### 2.8.4. Participants Found to Carry HBsAg

Figure 4 presents an algorithm illustrating the clinical management of HBsAg-positive mothers and HBsAg-positive children. Once the results of ALT, AST, and HBV DNA become available, HBsAg-positive participants will be referred to the district hospital; they will be examined by general physicians, who have been trained by hepatologists at the university hospital of Bobo-Dioulasso (Centre Hospitalier Universitaire (CHU) de Sourou Sanou). If ALT is elevated (>40 IU/L), the women will be further referred to CHU where the cause of ALT elevation is investigated. Women having both ALT >40 IU/L and HBV DNA >2000 IU/mL will immediately start anti-HBV therapy (generic of tenofovir disoproxil fumarate) for their own health and will be followed at the CHU every 3 months for the duration of at least 2 years. HBsAg-positive women who do not start treatment will be followed at the district hospital every 6 months. The women known to be co-infected with HIV will be referred to the National HIV Program. A 12 month follow-up will be carried out for HBsAg-positive children at the CHU if their ALT is >40 IU/L, and at the district hospital if their ALT is ≤40 IU/L.

### 2.9. Power Calculation

The power calculation was made for the primary endpoint: the prevalence of positive HBsAg in infants aged 9 months. The study will be carried out in the rural areas of the Dafra health district (8 CSPSs covering approximately 46,000 inhabitants) and Dô health district (16 CSPSs covering approximately 154,000 inhabitants) (Figure 2). At each step, we will have a 3-week interval to allow sufficient time to include the number of participants required per CSPS and per period. To obtain the highest possible statistical power, one cluster will be randomized for each step. The following assumptions were made:(a)The average number of live births in a catchment area covered by each CSPS is about 22 per month.(b)Infant death or lost to follow-up occurs in 10% of children by the age of 9 months.(c)The prevalence of HBsAg in pregnant women (P_HBsAg_) is estimated at 10%, but it can vary from 5% to 15% between the clusters [34].(d)The prevalence of HBeAg in HBsAg-positive pregnant women (P_HBeAg_) is estimated at 15%, but it can vary from 10% to 20% between the clusters [35].(e)With three doses of the pentavalent vaccine (8-12-16 weeks) without timely administration of HepB-BD, the risk of MTCT from HBsAg-positive and HBeAg-positive pregnant women (R_HBeAg-pos_) is 60% [20,36], and the risk from HBsAg-positive and HBeAg-negative pregnant women (R_HBeAg-neg_) is 5% [35].(f)With the timely administration of HepB-BD followed by three doses of pentavalent vaccine, the risk of MTCT from HBsAg-positive and HBeAg-positive pregnant women (R_HBeAg-pos-BD_) is 20% [18], and the risk from HBsAg-positive and HBeAg-negative pregnant women (R_HBeAg-neg-BD_) is 0% [35,37].

Using assumptions (a) and (b), the number of children evaluated at 9 months of age in each observation period (3 weeks) in each cluster (CSPS) was estimated at:*n* = (Average number of live births/CSPS/month) × (1 − lost to follow-up) × (3/4 weeks) = 14.8

Using assumptions (c), (d), (e), and (f), the incidence of HBV infection among the infants aged 9 months in the intervention (π_1_) and the control (π_0_) was estimated at:π_0_ = P_HBsAg_ × P_HBeAg_ × R_HBeAg-pos_ + P_HBsAg_ × (1 − P_HBeAg_) × R_HBeAg-neg_ = 1.33%
π_1_ = P_HBsAg_ × P_HBeAg_ × R_HBeAg-pos-BD_ + P_HBsAg_ × (1 − P_HBeAg_) × R_HBeAg-neg-BD_ = 0.30%

The coefficient of variation (CV) of the incidence of HBV infection in infants aged 9 months between control clusters (control observation periods) should be determined by the variation in the prevalence of HBV among pregnant women across the clusters. The prevalence of HBsAg in pregnant women is estimated to vary by a maximum of ±5% (5–15%), and the prevalence of HBeAg in HBsAg-positive pregnant women to vary by up to ±5% (10–20%) between the clusters. Consequently, the incidence of HBV infection in infants aged 9 months in the control periods would vary between 0.53% and 2.40% according to the CSPS, with a maximum variation of 1.07% around the estimated average of π_0_ = 1.33% (i.e., π_0_ ± 2SD = 1.33% ± 1.07%). The CV, the ratio of the standard deviation (SD) to the mean, was then estimated to be 0.40 in this study. Using the formula for the power calculation of the stepped wedge cluster randomized controlled trial [38], the study will have an 84% power to demonstrate that the intervention can reduce the incidence of HBV infection in infants aged 9 months, with a significance level of 5%. This corresponds to the inclusion of approximately 8500 mother–child pairs in a recruitment period lasting for 75 weeks (24 steps × 3 weeks + 3 weeks for the last period). Alternative scenarios were considered by varying the number of infants evaluated at the age of 9 months per cluster per period for the same number of participating CSPSs (Figure 5). This shows that the sample size of 13 children aged at 9 months/cluster/period provides a power of 80%.

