## 2. Methods

### 2.1. NéoVac Research Program

Neonatal Vaccination against Hepatitis B in Africa study (NéoVac), funded by the Total Foundation, is a research program originally started in 2015 in Senegal, Burkina Faso, and Madagascar, where the hepatitis B vaccination series have been scheduled at 6-10-14 weeks (Senegal and Madagascar) or 8-12-16 weeks (Burkina Faso), without HepB-BD. The aim of the program was to develop and evaluate a strategy to implement the timely administration of HepB-BD in these countries. The program was designed in two successive steps. Step 1, the formative phase, collects epidemiological, anthropological, and economic data in each country in order to develop a locally adapted, sustainable strategy for providing timely HepB-BD within 24 h of birth. This step is followed by Step 2 to evaluate the impact of the strategy to reduce the risk of HBV infection in infants. In Burkina Faso, Step 1 was conducted in Dafra District, Hauts-Bassins Region, in 2016–2017. The epidemiological study found approximately 90% of children born at health facilities, and 86% completed three doses of the pentavalent vaccine. The anthropological study observed that infant vaccination was widely accepted in the communities, and the economic study suggested that the costs of introducing HepB-BD would be relatively low compared to the introduction costs of other vaccines [23]. These results were presented at the steering committee organized by the study investigators in Ouagadougou on 20 Nov 2017, with local healthcare workers, researchers, civil society organizations, the Ministry of Health, and the WHO. Due to a high rate of institutional delivery in the study zone, the committee considered that the administration of HepB-BD in maternity services at health centers would result in good coverage of timely HepB-BD. However, the committee questioned to what extent the addition of HepB-BD would further prevent infant HBV infection. Consequently, the overall objectives of Step 2 were defined as follows: to assess the impact of adding HepB-BD to the current hepatitis B vaccination schedule at 8-12-16 weeks of life on the risk of MTCT, and to evaluate its acceptability among healthcare workers and community members, and its cost-effectiveness.

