#### 2.5.2. Individuals

All pregnant women of any age living in the area covered by the study CSPSs, who attended the antenatal care or gave birth at one of the study CSPSs, and who gave a written informed consent will be included. Exclusion criteria include a miscarriage, abortion, stillbirth, neonatal defect incompatible with life and any maternal or child health condition incompatible with the research activities. They will be also excluded if they had participated in other clinical trials that are incompatible with this trial.

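### The planned 14.8 evaluated infants per CSPS and period assumes that every live birth in the catchment is enrolled, and it does not fit the stated total of about 8,500 pairs

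*Protocol article*

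**What the plan says.** Assumption (a) in section 2.9 is a count of births in an area: "The average number of live births in a catchment area covered by each CSPS is about 22 per month". Assumption (b) is the only allowance for attrition: "Infant death or lost to follow-up occurs in 10% of children by the age of 9 months". The formula combines them as "Average number of live births/CSPS/month) × (1 − lost to follow-up) × (3/4 weeks) = 14.8", and the result is called the number of children evaluated at 9 months per cluster and period.

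Section 2.9 then states 84% power at a 5% significance level. It equates this with including about 8,500 mother–child pairs over 75 weeks, that is, 25 periods of 3 weeks in 24 CSPSs. It also reports one smaller scenario: "This shows that the sample size of 13 children aged at 9 months/cluster/period provides a power of 80" (percent).

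Section 2.5.2 defines who enters the trial: women living in the area "who attended the antenatal care or gave birth at one of the study CSPSs", and "who gave a written informed consent will be included". Pairs can still be excluded for a neonatal defect incompatible with life, an incompatible health condition, or participation in an incompatible trial. Section 2.8.1 adds that women under 18 need the consent of a legal representative.

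**The concern.** The formula starts from all births in the catchment and ends with evaluated study infants, but passes through only one loss, which occurs after birth. The step from birth to enrolled pair has no factor, which sets it at 100%. As worded, assumption (b) covers death and loss to follow-up. It does not cover refusals, women who are missed, women without CSPS contact, or exclusions.

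The counts also conflict. The number evaluated cannot exceed the number included, yet the printed n multiplied over all cluster-periods is larger than the stated inclusions.

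At stake is the power figure for the primary endpoint. A reader cannot tell that 84% depends on nearly universal enrolment, or what level of enrolment the trial must reach to keep 80%.

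**Working it through.** **Inputs, all from section 2.9.** 22 live births per CSPS and month; 10% loss; factor 3/4; I = 24 clusters; T = 25 periods; one cluster crossing per step; CV 0.40; 5% significance, taken as two-sided because sidedness is not stated.
- π0 = 0.10 × 0.15 × 0.60 + 0.10 × 0.85 × 0.05 = 1.325%
- π1 = 0.10 × 0.15 × 0.20 = 0.30%

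**Step 1: the plan's n.** 22 × 0.90 × 0.75 = 14.85, which agrees with 14.8. The product leaves no room for a further factor, so the enrolled fraction is 1. Over 24 × 25 = 600 cluster-periods this means 22 × 0.75 × 600 = 9,900 births, all enrolled, and 14.85 × 600 = 8,910 evaluated (8,880 with n = 14.8).

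**Step 2: the plan's power.** The Hussey and Hughes variance for a stepped wedge is

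Var = I·s²(s² + T·τ²) / [(I·U − W)s² + (U² + I·T·U − T·W − I·V)τ²],

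with s² = π0(1 − π0)/n and τ = 0.40 × π0 = 0.0053.
- For this layout U = 300 and W = V = 4,900. So I·U − W = 7,200 − 4,900 = 2,300, and the second bracket is 90,000 + 180,000 − 122,500 − 117,600 = 29,900.
- At n = 14.8: s² = 0.013074/14.8 = 0.000883 and τ² = 0.00002809, so Var = 0.0000117 and the standard error is 0.00342.
- Power = Φ(0.01025/0.00342 − 1.96) = 85.0%, against the stated 84%.
- At n = 13 the same formula gives 80.9%, against the stated 80%.

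Both are within about one point, so the formula is a fair stand-in for the plan's own method.

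**Step 3: add an enrolled fraction f.** n = 22 × f × 0.90 × 0.75. The documents give no f, so the values are assumptions.

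| f | n per cluster-period | evaluated in total | power |
|---|---|---|---|
| 100% | 14.85 | 8,910 | 85.1% |
| 95% | 14.1 | 8,464 | 83.5% |
| 90% | 13.4 | 8,019 | 81.8% |
| 85% | 12.6 | 7,573 | 79.9% |
| 80% | 11.9 | 7,128 | 77.9% |
| 70% | 10.4 | 6,237 | 73.1% |

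On this formula 80% power needs n of about 12.65, or 12.65/14.85 = 85% of births enrolled. On the plan's own 80% point of 13, it needs 13/14.85 = 87.5%.

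**Step 4: the two readings of 8,500.**
- *Evaluated pairs:* 8,500/600 = 14.17 per cluster-period and 83.7% power. The implied enrolled fraction is 8,500/8,910 = 95%.
- *Included pairs, 10% then lost:* 8,500 × 0.90 = 7,650 evaluated; 7,650/600 = 12.75 per cluster-period and 80.3% power. The implied enrolled fraction is 8,500/9,900 = 86%.

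Neither reading returns 14.8.

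**The case against.** The case for leaving the calculation alone has real force.

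- **Enrolment may well be high.** Step 1 found about 90% facility births. Home births remain eligible through antenatal attendance, and women arriving without antenatal care are invited after delivery. Nothing in the article puts the enrolled fraction below the 85–88% at which power drops under 80%. This stands, and it is why only a range can be given.
- **The effect is small and partly shown.** At 90–95% enrolment the figure moves by one or two points, and the n = 13 scenario already shows the cost of a 12% shortfall. This stands too, but the article does not link that scenario to incomplete enrolment.
- **The variance choice is conservative.** With variance at the average of the two risks, power would be 95.7% at n = 14.8 and still 91.8% at n = 11.9. That version does not reproduce the stated 84%, so it cannot defend that figure. It does argue against calling the trial underpowered.
- **The article is condensed.** An uptake rate may be in the full protocol. The point therefore rests on the printed formula and totals, not on a missing consent rate. The word approximately may also cover part of the gap between 8,880 and 8,500, but not the question of which count is meant.

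Two stronger readings are tempting and are not supported. A reader might infer from the Step 1 result, "approximately 90% of children born at health facilities, and 86% completed three doses of the pentavalent vaccine", that 90% retention at 9 months is unrealistic. But completing a three-dose series is not attendance at 9 months: a child who missed a dose can still attend. If the 86% refers to all children, combining it with an enrolled fraction could also count the same children twice. A reader might also infer that the assumed risks belong to a different population from the one enrolled. The documents do not show that; only the count is in question.

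**Conclusion.** The point holds as an unstated and optimistic assumption, not as an arithmetic slip: the multiplication in section 2.9 is correct. The printed n treats every catchment birth as an enrolled pair, contrary to section 2.5.2, and the 84% power needs about 95–100% enrolment. Separately, 8,880 evaluated infants cannot come from about 8,500 included pairs.

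The likely effect is modest: roughly 78–82% power for 80–90% enrolment, and about 80% if 8,500 are included and 10% are lost. These figures rest on an assumed enrolled fraction, on all other inputs as printed, and on a two-sided test with variance at the control risk, which is the version that reproduces the plan. They do not show that the trial is underpowered. They show that the stated power has little margin above 80% and that the article does not say what that margin depends on.

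**What to change.** In section 2.9, write n = live births × enrolled fraction × (1 − loss) × period length, where the enrolled fraction covers CSPS contact, consent and exclusions. State its assumed value and the basis for it. Say whether the 8,500 are included or evaluated pairs, and make that total agree with n × 600. Then restate n and power by the plan's own method, with a short range over the enrolled fraction, and tie the existing n = 13 scenario to the enrolment level it represents.

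The cost is a few lines of text and one recalculation. Stated power falls slightly. The restatement itself calls for no extra enrolment and no change to trial procedures, and it gives the sponsor an enrolment threshold to monitor.

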### 2.12. Statistical Methods

Using an intention-to-treat analysis involving all mother–child pairs included in the study, the impact of introducing monovalent hepatitis B vaccines at birth on the risk of MTCT will be estimated by comparing the proportion of children positive for HBsAg at the age of 9 months between two groups: children born before the introduction of HepB-BD into their CSPS (control arm) and those born after their CSPS begins HepB-BD (intervention arm), regardless of whether or not they have received HepB-BD according to the assignment of the intervention to their CSPS. Our primary analysis will be “complete case analysis” excluding those with missing outcomes as it is unlikely that maternal HBV infection, the leading factor for the vaccine failure, is related with a loss to follow-up [40,41]. We will also conduct a sensitivity analysis with an extreme assumption that all those lost to follow-up were infected with HBV.

A per-protocol analysis will also be performed by restricting the analysis to children born before the introduction of HepB-BD into their CSPS and not having received HepB-BD, or to those born after the introduction of HepB-BD into their CSPS and who have received HepB-BD. To account for the calendar time and for the correlations between individuals within the same cluster, a logistic regression model with a random effect for clusters and a fixed effect for each step will be fitted [25]. All the analyses will be performed using STATA^®^.

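### The control-versus-intervention risks behind the 84% power assume that every intervention-period infant gets a timely birth dose, whereas the primary analysis is intention-to-treat

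*Protocol article*

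**What the plan says.** Assumption (f) in Section 2.9 sets the transmission risks in the intervention periods. It reads "With the timely administration of HepB-BD followed by three doses of pentavalent vaccine, the risk of MTCT" and gives 20% for infants of HBeAg-positive mothers and 0% for infants of HBsAg-positive, HBeAg-negative mothers. The formula for π1 applies these risks to all intervention-period infants and has no coverage term, which gives 0.30% against a control risk of 1.33%. On this basis "the study will have an 84% power to demonstrate that the intervention can reduce the incidence of HBV infection in infants aged 9 months". The only sensitivity analysis described varies the number of infants per cluster and period: "the sample size of 13 children aged at 9 months/cluster/period provides a power of 80" per cent.

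Section 2.12 makes the primary comparison intention-to-treat by the period in which the infant's health center stood at birth, "regardless of whether or not they have received HepB-BD according to the assignment of the intervention to their CSPS".

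On delivery, Section 2.1 reports from Step 1: "The epidemiological study found approximately 90% of children born at health facilities, and 86% completed three doses of the pentavalent vaccine". Section 2.6.3 says that infants born at home "will receive HepB-BD at the first contact with the CSPS at any time up to the time when the next dose" is due, which is at 8 weeks. Section 2.7.2 lists birth-dose coverage and timeliness as a secondary outcome.

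**The concern.** The effect used for planning is the effect of a timely birth dose in infants who all receive it. The effect to be estimated is that of introducing the service, which late and missed doses dilute. Even if the vaccine performs exactly as assumed, the intention-to-treat contrast will be smaller than the one entered in the power calculation.

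Two things are at stake. The 84% is presented as the power for the primary endpoint, but it describes a delivery scenario that the protocol does not expect. And because no intention-to-treat target is stated, a result weaker than a 77% reduction could be read as lower vaccine effect when part of the gap is incomplete delivery.

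**Working it through.** **Inputs from Section 2.9.** HBsAg prevalence 10%; HBeAg prevalence among HBsAg-positive women 15%; transmission risks 60% and 5% (control), 20% and 0% (timely birth dose); 14.8 infants per cluster and period; between-cluster CV 0.40; 24 clusters, one per step, and 25 periods ("24 steps × 3 weeks + 3 weeks for the last period"). The test is "with a significance level of 5" per cent; sidedness is not stated, and two-sided is assumed here.

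**Risks.**
- π0 = 0.10 × 0.15 × 0.60 + 0.10 × 0.85 × 0.05 = 1.325% (stated 1.33%).
- π1 = 0.10 × 0.15 × 0.20 + 0 = 0.30% (as stated). This is exactly the value at 100% timely coverage. The ratio is 0.30/1.325 = 0.23, a 77% reduction.

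**Reproducing the stated power.** The Hussey–Hughes closed form was used with I = 24, T = 25, σ² = π0(1 − π0)/n and τ = CV × π0.
- Design sums: U = 300, W = 4900, V = 4900. Hence IU − W = 2300 and U² + ITU − TW − IV = 29,900.
- σ² = 0.01325 × 0.98675/14.8 = 0.000883; τ² = (0.40 × 0.01325)² = 0.0000281.
- Var = Iσ²(σ² + Tτ²)/[2300σ² + 29,900τ²], so SE = 0.00342.
- Power = Φ(0.01025/0.00342 − 1.96) = 85.0%. At n = 13 it is 80.9%.

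The plan states 84% and 80%, so its figures are reproduced to within about one point.

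**Adding coverage.** Let c be the share with a timely dose, and let the others keep the control risk: π1(c) = c × 0.30% + (1 − c) × 1.325%. All else is unchanged, with n = 14.8.

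| Timely coverage c | π1(c) | Ratio to π0 | Power, closed formula |
|---|---|---|---|
| 100% | 0.300% | 0.23 | 85.0% |
| 95% | 0.351% | 0.27 | 81.2% |
| 90% | 0.402% | 0.30 | 76.9% |
| 80% | 0.505% | 0.38 | 66.9% |

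The formula falls below 80% once c is under about 93.5%. If a late dose keeps half the benefit (an assumption) and every infant without a timely dose gets one late, 90% coverage gives 0.351% and 81.2%, and 80% coverage gives 0.402% and 76.9%.

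**How far the formula represents the planned analysis.** It works on the risk difference and uses the control-period variance in every cell. That overstates the variance, because intervention-period risks are much lower. With the variance taken at the mean of the two risks, the same formula gives 95.7% at full coverage, 89.7% at 90% and 79.9% at 80%. Simulation of the planned logistic model (random cluster effect with CV 0.40, fixed step effects, several hundred runs per scenario) gives:
- 98–99% at the plan's inputs;
- 94–95% at 90% coverage with n = 14.8;
- 92–93% at 90% coverage with n = 13.7;
- 82–84% at 80% coverage with n = 13.7.

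The smaller n is 22 × 0.9 × 3/(52/12) = 13.7, which counts a month as 52/12 weeks rather than 4. It serves here only as a less favourable cell size.

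**The case against.** The strongest reply is that the trial keeps adequate power. This stands: for the planned model, power is about 95% at 90% timely coverage and still above 80% at 80% coverage with no benefit from late doses. A reader of the table might infer that the trial is underpowered, but the falls to 77% and 67% belong to a conservative formula and not to the planned analysis.

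The coverage figures are also soft. The 90% is facility birth, not timely vaccination, and comes from Dafra only, while 16 of the 24 centers are in Dô. Women enter the trial through antenatal care or delivery at a study center (Section 2.5.2), so coverage among participants could exceed 90%. The 80% has no source in the protocol. Zero benefit from a late dose is a worst case, since the Introduction cites a study in which risk rose by age group at first dose. These points justify a range; they do not justify 100%.

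Two further readings are tempting and fail. First, one might say that 0.30% is the per-protocol risk. The per-protocol set in Section 2.12 requires only that the dose was received, not that it was timely, so 0.30% describes a stricter condition than per-protocol. Second, one might set the planned ratio of 0.23 against the relative risk of 0.28 in the Introduction and call assumption (f) too optimistic. That 0.28 compares a series starting at birth with no vaccine, whereas this trial's control infants receive three doses. The 0.23 is itself a blend of 20%/60% = 0.33 and 0%/5% = 0. Whether (f) is optimistic is separate from coverage and rests on cited sources that cannot be judged from the protocol.

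**Conclusion.** The mismatch is real. The arithmetic in Section 2.9 is right, but 84% is the power at full timely coverage and not for the intention-to-treat contrast that is primary. With facility birth standing in for timely dosing (90%) and no benefit from late doses, the expected intervention risk is about 0.40% rather than 0.30%, and the expected reduction about 70% rather than 77%. On the closed formula the cost is about 4 to 8 points of power at 90% coverage, depending on whether late doses keep half the benefit or none.

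This does not threaten the trial, because the planned model has margin over that formula. The result assumes that the stated transmission risks and CV hold and that the test is two-sided. The three-dose pentavalent completion rate of 86% was not varied, since the protocol gives no risk for an incomplete series. Severity is minor to moderate: a stated figure needs correcting, but the design does not.

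**What to change.** - Replace π1 by a coverage-weighted value: 0.9 × 0.30% + 0.1 × 1.325% = 0.40% as the base case. Add rows for 80% and 95% coverage and for partial benefit from late doses.
- State the expected intention-to-treat effect: a risk ratio, and practically the same odds ratio, of about 0.30 at 90% coverage.
- Restate the power for the planned logistic mixed model by simulation, and say whether the test is one- or two-sided.
- Describe 0.30% as the risk under full timely coverage, not as the per-protocol assumption.

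The cost is one recalculation and a short table. Sample size, number of centers, recruitment period and conduct stay as they are.
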